#### Intensive smoking intervention using CBT

Participants in the intensive smoking intervention arm will receive 12 weeks of NRT plus weekly individual smoking cessation counseling sessions for the first 3 months, followed by monthly group sessions for the next 3 months. In addition, they will receive the brief alcohol counseling also provided to the UC participants. CBT strategies will be employed to identify and address smoking triggers and to employ urge reduction strategies, including delay, escape, avoid, distract and substitute. The key intervention strategies will also include introducing self-monitoring of smoking behavior, completing a functional analysis of smoking using a smoking “wrap sheet,” developing a specific quit plan, enlisting allies and relapse prevention. The participants will be asked to quit after their fourth counseling session [41].

#### Usual care (brief smoking cessation and brief alcohol counseling, both based on USPHS guidelines)

In the UC condition, participants will receive NRT as described above for the IS intervention and brief (20 min), one-time counseling for smoking and alcohol cessation. The smoking cessation counseling will be based on the “five A’s” model (ask, advise, assess, assist, arrange) recommended in the USPHS clinical practice guidelines [34]. Consistent with these guidelines, counselors will carry out the following procedures: (1) congratulate the participant on enrolling in the study, (2) describe the harms related to smoking and the benefits of quitting, (3) advise the participant to quit immediately, (4) assist participants to set a quit date, (5) encourage participants to tell friends and family about their quitting and (6) describe potential relapse situations and other barriers to quitting. The brief alcohol counseling will follow USPHS guidelines [42] and includes elements such as (1) presenting screening results, (2) identifying risks, (3) discussing consequences, (4) soliciting commitment, (5) identifying goals and (6) giving advice and encouragement. At the end of the session, participants interested in additional smoking or alcohol interventions will be referred to local and national treatment programs. We will measure participants’ engagement in smoking cessation or alcohol programs outside the study as potential moderators of intervention effects.

### Study procedures

#### Individual session 1

The first session will begin at baseline after enrollment. This visit will last up to 90 minutes, whereas most other visits will last 30–60 minutes, depending on to which group the participant is assigned. Ground rules will be established at the first counseling session; participants will also be informed that each counseling session will be audio-recorded before the commencement of the session. CO testing and an alcohol breathalyzer test will be conducted at all individual sessions. The UC group will receive a brief, one-time advice session on smoking cessation and alcohol use. Participants will receive a $20 gift card, tote bag and two bus tokens at this session as compensation for their time.

#### Individual sessions 2–12

Session counseling procedures for the IS and IntS+A conditions will follow the same format as the first session. At all sessions, a survey will be administered by the community mobilizer before the counseling session begins. Additionally, participants will be asked about their smoking history and/or drinking patterns, as well as craving, depending on the CBT arm to which they were randomized. Task assignments, within-session role playing, coping skills training, identification of cognitive and environmental antecedents, behavioral choices and consequences, and both past and future high-risk situations will be carried out during the CBT counseling sessions. A quit date will be set in the smoking arm at week 4. NRT (nicotine patch plus gum or lozenge) will also be carried out for 12 weeks starting at week 4. The estimated session durations are 30 minutes for the IS group and 60 minutes for the IntS+A arm.

#### Group sessions 17–25

After the week 16 survey, participants in the CBT groups will be asked to return for booster group sessions for 3 months. Reminder calls will be made during the week to each participant. Participants will be asked to complete the weekly survey at their arrival. They will be encouraged to discuss their abstinence status and about the day-to-day challenges they encounter. The research counselors will ensure that the environment is comfortable for the participants and conducive to their expressing themselves. Procedures for the group will follow the CBT format covered during the individual sessions. All group counseling sessions will be cofacilitated by trained study and homeless shelter staff. Participants will receive a $10 gift card and two bus tokens for as compensation for their time. The estimated duration of the sessions is 30–60 minutes.

#### Weeks 26 and 52 follow-up

Participants will be asked to return at 6 months and 12 months postbaseline to participate in an outcome survey and cotinine analysis to verify abstinence status. After collection of samples and assessment, participants will be asked about the study program and how to improve it. Participants will receive $50 for participation at week 26 and $75 for week 52. Each visit will take approximately 60–90 minutes.

### Outcomes

The primary smoking outcome is cotinine-verified 7-day smoking abstinence at follow-up week 52, and the primary alcohol outcome will be breathalyzer-verified 90-day alcohol abstinence at week 52. Exploratory aims are to evaluate (1) how smoking cessation or reduction relates to psychosocial factors such as levels of depression, hopelessness and perceived stress at weeks 12, 26 and 52 of follow-up; (2) how alcohol abstinence or reduction relates to psychosocial factors such as levels of depression, hopelessness and perceived stress at 12, 26 and 52 weeks of follow-up; (3) how treatment outcomes relate to history of other substance abuse; (4) how treatment outcomes relate to opportunities for employment and housing, as well as overall health and well-being; and (5) participants’ perceptions of the acceptability and usefulness of components of the various interventions. Additional aims include identifying potential impacts on intervention efficacy of psychosocial factors such as depression, hopelessness and perceived stress; other substance abuse; changes in employment and housing; and overall health.

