**Fig. 1 Fig1:**
[figure not shown]
Flowchart of the Enhancing Smoking Cessation in the Homeless Population study. *CBT* cognitive behavioral therapy, *NRT* nicotine replacement therapy, *LTFU* long-term follow-up, *SC+A* combined smoking cessation and alcohol

Counseling using CBT follows a protocol used in a recent study of alcohol-dependent smokers [36–38]. During the first 3 weeks after enrollment, CBT counseling sessions will focus on the participants’ preparation for their quit date, on which they will receive the NRT. Participants randomized to the IS will receive brief alcohol counseling plus 12 weekly CBT counseling sessions, starting at their baseline visit, that are 20–30 minutes in length. Last, participants randomized to the IntS+A group will receive 12 weekly CBT counseling sessions beginning at their baseline visit, each of which are approximately 50–60 minutes in length. The study design does not include a placebo arm, owing to ethical concerns. The primary smoking outcome is cotinine-verified 7-day smoking abstinence at follow-up week 52, and the primary alcohol outcome will be breathalyzer-verified 90-day alcohol abstinence at follow-up week 52. The secondary smoking outcome will be prolonged smoking abstinence at weeks 12, 26 and 52 with CO verification at weeks 12 and 26. CO is used for verification at these times because cotinine verification is not useful in the context of NRT. The secondary alcohol outcome will be self-reported continuous alcohol abstinence for 30 days at weeks 12 and 26 and for 90 days at week 52.

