### Participants

A total of 645 participants will be enrolled in the study (Fig. 2). Final follow-up for each participant will be at week 52 of their participation in the trial. Participants will be randomized into one of three groups: UC (*n* = 215), IS (*n* = 215) or IntS+A (*n* = 215). Eligibility criteria are (Table 2) currently homeless [21], current daily cigarette smoker, aged 18 years or older, willing to use NRT (nicotine patch and gum or lozenge) for 12 weeks, willing to participate in counseling sessions for 12 weeks and willing to complete 16 total appointments (12 weekly counseling visits, 3 monthly group counseling visits and 1 retention visit) over the 52-week study period. The determination of participants’ homelessness will be based on the Stewart B. McKinney Act, passed by the U.S. Congress in 1987, in which *homelessness* is defined as “any individual who lacks a fixed, regular and adequate nighttime residence” or “one whose primary nighttime residence is a supervised publicly or privately operated shelter designed to provide temporary living accommodations, transitional housing, or other supportive housing program or a public or private place not meant for human habitation (e.g., on the streets or in abandoned buildings, tents, or automobiles)” [4, 9, 21]. Participants will also be considered to be homeless if they have been residing with family or friends for a period of 3 months or less. *Current smoking* is defined as smoking at least one cigarette per day in the previous 7 days and having smoked at least 100 cigarettes in the participant’s lifetime. To confirm their smoking status, participants will be asked to take an exhaled CO test with a reading of at least 5 parts per million, based on recommendations of the Society for Research on Nicotine and Tobacco [22–24].

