### Statistical analyses and sample size and power calculations

For this study, 645 participants will be randomized at baseline to test the main effects of smoking and alcohol interventions for the primary smoking outcome (cotinine-verified 7-day smoking abstinence at week 52 follow-up) and alcohol outcome (breathalyzer-verified continuous alcohol abstinence for 90 days at week 52 follow-up). The study is powered to test the primary hypotheses using χ^2^ tests and the secondary hypothesis using Fisher’s exact test. Assuming a two-sided χ^2^ test with a type I error rate of 0.025 for each of two primary outcomes, smoking abstinence rates of 18 % in the IntS+A group versus 8 % in the IS group and 4 % in the UC group, a sample size of 215 participants in the IntS+A group and 430 participants in the IS and UC combined group will achieve a power of 80 %. With 645 participants and a type I error rate of 0.025, we have greater than 90 % power for the primary alcohol hypothesis, assuming 90-day alcohol abstinence rates of 32 % vs. 10 % for the IntS+A group versus the IS intervention or UC groups . Assuming a two-sided Fisher’s exact test with a type I error rate of 0.05 for the secondary outcome of smoking abstinence rate of 12 % in the IntS group versus 4 % in the UC group, a sample size of 215 participants per group will achieve a power of 82 %. Our sample size calculation was based on the analysis that classified those lost to follow-up as smokers or drinkers and therefore has accounted for up to a 25 % attrition rate observed in the prior Power to Quit (PTQ) study [32, 33].

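### The primary alcohol outcome is labelled breathalyzer-verified over 90 days, but the described schedule puts at most one breath test in that window, so it can disprove abstinence but not verify it

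*Protocol article*

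**What the plan says.** The Outcomes section defines the alcohol primary as "breathalyzer-verified 90-day alcohol abstinence at week 52". The Abstract, the Overview of study design and the Discussion use the same label. The section on sample size and power makes it stricter: "breathalyzer-verified continuous alcohol abstinence for 90 days at week 52 follow-up". That section gives this outcome a two-sided type I error of 0.025, half of the total.

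The Overview of study design, in the text after Fig. 1, also names a secondary alcohol outcome: "self-reported continuous alcohol abstinence for 30 days at weeks 12 and 26 and for 90 days at week 52".

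On timing, Study procedures (Individual session 1) says that "CO testing and an alcohol breathalyzer test will be conducted at all individual sessions". The follow-up section covers weeks 26 and 52, and gives the purpose of those visits as to "participate in an outcome survey and cotinine analysis to verify abstinence status"; no breath test is named there. The Participants section counts "16 total appointments (12 weekly counseling visits, 3 monthly group counseling visits and 1 retention visit" over the 52 weeks and does not date the retention visit.

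Under Analyses for primary hypotheses, participants lost to follow-up count as drinkers and the outcome is compared by χ² test. That section attaches biochemical verification to the smoking outcome only.

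**The concern.** Calling an outcome verified tells the reader that an objective measurement confirms it over the period claimed. For smoking, the article pairs cotinine with a 7-day window. For alcohol, it pairs a breath test with 90 days in parallel wording, as though the two were equally confirmed.

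If only one breath test falls in the window, the primary alcohol outcome differs from the self-reported secondary at week 52 only by that test. Participants cannot be unaware of their counselling. The integrated arm (IntS+A) receives 12 weekly sessions with a 30-minute alcohol segment, while the intensive smoking (IS) and usual care (UC) arms receive brief alcohol counselling. Over-reporting of abstinence may therefore differ by arm, in the direction of the hypothesis. A positive result could then partly reflect reporting and yet be published as verified abstinence.

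**Working it through.** **1. The plan's own figure.** Inputs from the sample size section: 32 % vs 10 %, two-sided α = 0.025 (critical z = 2.2414), 215 vs 430.
- Pooled rate: (215 × 0.32 + 430 × 0.10)/645 = 0.1733.
- Standard error under the null: √[0.1733 × 0.8267 × (1/215 + 1/430)] = 0.03162.
- Standard error under the alternative: √[0.32 × 0.68/215 + 0.10 × 0.90/430] = 0.03495.
- Power: Φ[(0.22 − 2.2414 × 0.03162)/0.03495] = 0.99999. With 215 vs 215 it is 0.9998.

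Both agree with the stated figure of more than 90 %. The power statement is not in question; what the outcome measures is.

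**2. Breath tests inside the window.** Week 52 is day 364, so the window opens about day 364 − 90 = 274, or week 39. The 12 weekly individual sessions and the booster groups (headed as sessions 17–25) lie before it, and so does week 26 (day 182). That leaves week 52. The follow-up section names no breath test there; I assume one is taken, because the outcome definition needs it.

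**3. What one test covers.** The documents give no detection time, so I assume 6, 12 or 24 hours.
- Share of 90 days (2,160 hours): 6/2160 = 0.28 %; 12/2160 = 0.56 %; 24/2160 = 1.1 %.
- Chance of a positive test in someone who drank on k of 90 days, with timing unrelated to the visit: (k/90) × (hours/24). For k = 10 this is 2.8 %, 5.6 % or 11 %. For k = 45 it is 12.5 %, 25 % or 50 %.

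**4. Effect of differential misreporting (illustration).** Assume true abstinence of 10 % in every arm, the plan's comparator rate. Let f be the share of IntS+A drinkers, and g the share of IS and UC drinkers, who falsely report abstinence undetected. Observed rates are 0.10 + 0.90f and 0.10 + 0.90g. Where 25 % of IntS+A is lost and all of those lost are counted as drinkers, only 65 % of the arm can misreport, so its rate is 0.10 + 0.65f. Rejection rates come from exact binomial enumeration of the pooled χ² test, 215 vs 430, at 0.025.

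| f | IS and UC honest, no loss | IS and UC honest, 25 % of IntS+A lost |
|---|---|---|
| 0 | 2.5 % | 2.5 % |
| 2 % | 6.9 % | 4.9 % |
| 5 % | 29.8 % | 16.8 % |
| 8 % | 63.8 % | 38.5 % |
| 10 % | 81.8 % | 55.2 % |

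With f = 5 % (observed rate 14.5 %, about 0.05 × 0.90 × 215 ≈ 10 people) and no loss:

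| g | Rejection |
|---|---|
| 0 | 29.8 % |
| 2 % | 11.0 % |
| 3 % | 6.0 % |
| 5 % | 2.5 % |

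Only the difference between arms moves the error rate.

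**5. A tipping point in counts.** With 43 of 430 comparators abstinent (10 %), 34 of 215 in IntS+A gives χ² = 4.61 and 35 gives 5.32, against a critical value of 5.02. Significance needs 35, where 21.5 are expected under no effect. About 13 to 14 false reports would be enough.

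**The case against.** The strongest reply is that this article condenses a fuller protocol. Figs. 1 and 2 are not shown and the retention visit has no date, so a breath test between weeks 39 and 52 cannot be ruled out. That stands: the absence of earlier tests in the window, and the presence of one at week 52, are both inferences from the visible text. A reader might infer that no breath test is taken at week 52; the documents do not support that either.

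Second, the article does not hide self-report. It lists it as a secondary outcome, and its analysis section does not call the alcohol outcome biochemically verified. This also stands. The overstatement lies in the label used in the outcome definitions, and the breath test still catches very recent drinking.

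Third, IS and UC participants also receive alcohol counselling that seeks commitment and sets goals, so they may over-report too. Those lost to follow-up cannot misreport at all. Both points are right, and both lower the error, as the tables show. A reader might take the highest figures as the trial's actual false-positive rate. They are not; no misreporting rate is given in the documents.

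Fourth, a reader might infer that assessors are unblinded. The article describes no masking, but the full protocol may, so the point rests only on participants knowing their arm. Likewise, the lack of a tipping-point analysis is no fault here, since that is ordinary SAP content; it is offered only as a remedy.

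**Conclusion.** The concern holds as a mismatch between a primary outcome's label and the design described. On the visible text, at most one breath test falls in the 90-day window. Under a 6 to 24 hour detection assumption it covers about 0.3 to 1.1 % of that window, so it can refute abstinence but cannot confirm it. Nothing in the χ² test or the Bonferroni split addresses differential reporting. Counting losses as drinkers limits it but does not remove it.

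The size depends on unknown reporting behaviour. At 5 % false reports in IntS+A, the error ranges from nominal (equal misreporting) through 11 % and 17 % to about 30 % (honest comparators, no loss). It would be too strong to say that the result will be biased, or that the outcome is worthless. Self-reported abstinence is a legitimate endpoint; describing it as verified for 90 days is what the design does not support. The change should be made, because it alters what may be concluded on one of the two primary outcomes.

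**What to change.** 1. In the Abstract, Overview of study design, Outcomes, sample size section and Discussion, restate the primary alcohol outcome as self-reported 90-day abstinence at week 52, with a positive week-52 breath test counting as drinking. Name that test among the week-52 procedures. Do not describe the result as verified 90-day abstinence.
2. Add a tipping-point analysis: report how many IntS+A self-reported abstainers would have to be reclassified as drinkers for significance at 0.025 to be lost.
3. Optionally, have participants complete the week-52 drinking items themselves in the existing REDCap survey.

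The test, α and sample size do not change, and no new visit or biomarker is needed. The cost is a weaker but accurate claim and one extra sensitivity analysis. The Trial status section puts recruitment in its first phase, so the wording can still be settled before most week-52 data exist.

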### Participant incentives

Participants will be compensated with non-monetary incentives such as tote bags, bus tokens, stress balls, pens and water bottles after taking the eligibility survey. At enrollment, each participant will receive a $20 debit card serviceable at any automated teller machine within the United States, in addition to other small gift items, such as playing cards, $5 Subway gift cards, bus tokens and tote bags. Participants will receive $50 for participation at week 26 and $75 for week 52. For all other visits completed, participants will receive monetary incentives of $10. Participating shelters will also be compensated up to $1000/year for their assistance with recruitment and retention. Shelters will receive separate payments for their therapists who participate in training ($25/h) and cofacilitate the group counseling sessions ($50/h).

### Data management

Data management for this project will encompass data entry, data cleaning, identifying and tagging any crossovers and conversion into proper format for data analysis and recoding. REDCap (Research Electronic Data Capture; http://project-redcap.org/), a secure web application for building and managing online surveys and databases, will be used for design, implementation and maintenance of the database. In addition, a computer-based tracking system will be developed to follow each patient and to prompt the staff regarding the upcoming data collection point. Data collection points for each subject will be calculated from his or her initial date of contact. Before data collection, the study protocol was approved and monitored by the University of Minnesota’s Institutional Review Board.

### Statistical analyses and sample size and power calculations

For this study, 645 participants will be randomized at baseline to test the main effects of smoking and alcohol interventions for the primary smoking outcome (cotinine-verified 7-day smoking abstinence at week 52 follow-up) and alcohol outcome (breathalyzer-verified continuous alcohol abstinence for 90 days at week 52 follow-up). The study is powered to test the primary hypotheses using χ^2^ tests and the secondary hypothesis using Fisher’s exact test. Assuming a two-sided χ^2^ test with a type I error rate of 0.025 for each of two primary outcomes, smoking abstinence rates of 18 % in the IntS+A group versus 8 % in the IS group and 4 % in the UC group, a sample size of 215 participants in the IntS+A group and 430 participants in the IS and UC combined group will achieve a power of 80 %. With 645 participants and a type I error rate of 0.025, we have greater than 90 % power for the primary alcohol hypothesis, assuming 90-day alcohol abstinence rates of 32 % vs. 10 % for the IntS+A group versus the IS intervention or UC groups . Assuming a two-sided Fisher’s exact test with a type I error rate of 0.05 for the secondary outcome of smoking abstinence rate of 12 % in the IntS group versus 4 % in the UC group, a sample size of 215 participants per group will achieve a power of 82 %. Our sample size calculation was based on the analysis that classified those lost to follow-up as smokers or drinkers and therefore has accounted for up to a 25 % attrition rate observed in the prior Power to Quit (PTQ) study [32, 33].

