#### Basis for sample size

We based our estimates for the main outcomes on data from our previous PTQ study among homeless smokers, as well as from the available literature [38, 43]. In the PTQ study, 7-day abstinence rates at week 26 were 9.3 % for the MI+NRT condition and 5.1 % for the control group. In another study [43] of alcohol-dependent smokers, our research team reported 7-day abstinence rates at 6 months as 9.1 % and 2.2 % for an intensive smoking intervention (three counseling sessions + NRT) and brief advice, respectively. We therefore projected the smoking abstinence rates as 4 % for the UC condition and 12 % for the IS condition. Our PTQ study also showed that the smoking abstinence rate for those who quit drinking during the study was nearly double that for drinkers, despite not having an alcohol intervention. We conservatively projected the smoking abstinence rate for the IntS+A condition as 18 %. We based the projection for the alcohol abstinence rates on a study [38] in which our research team found 90-day alcohol abstinence rates of 32–43 % at 12 months among alcohol-dependent smokers.

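### The IS arm is planned at both 8 % and 12 % week-52 smoking abstinence; the stated 82 % secondary power holds only at 12 %, and the stated 80 % primary power fits the described comparison at neither rate

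*Protocol article*

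**What the plan says.** All the figures concern cotinine-verified 7-day smoking abstinence at week 52.

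- **Primary contrast** (Statistical analyses and sample size and power calculations). The test is fixed by "Assuming a two-sided χ^2^ test with a type I error rate of 0.025 for each of two primary outcomes". The assumed rates are "smoking abstinence rates of 18 % in the IntS+A group versus 8 % in the IS group and 4 % in the UC group". The result is that "215 participants in the IntS+A group and 430 participants in the IS and UC combined group will achieve a power of 80" %.
- **Secondary contrast** (same paragraph). The test is fixed by "Assuming a two-sided Fisher’s exact test with a type I error rate of 0.05 for the secondary outcome", with a "smoking abstinence rate of 12 % in the IntS group versus 4 % in the UC group", and "a sample size of 215 participants per group will achieve a power of 82" %. No arm is called IntS. The section Analyses for primary hypotheses makes clear that the Fisher comparison is between IS and UC, so the 12 % belongs to IS.
- **Source of the rates** (Basis for sample size). "We therefore projected the smoking abstinence rates as 4 % for the UC condition and 12 % for the IS condition". For the third arm: "We conservatively projected the smoking abstinence rate for the IntS+A condition as 18" %.

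Participants lost to follow-up count as smokers, so the rates apply to all 215 randomized per arm and no further allowance for dropout is needed in the check.

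**The concern.** One arm, one outcome and one visit carry two planning rates. The 8 % appears once, in the primary power statement, and no source is given for it. The 12 % appears twice and is the only IS value that the basis section derives.

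The choice matters because the two power figures respond to the IS rate in opposite directions. A lower IS rate widens the gap between IntS+A and its comparator and narrows the gap between IS and UC. The article says that the study is powered for both the primary and the secondary hypothesis. If 8 % were the real assumption, that would not be so for IS versus UC, and a null result there would say little.

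The 80 % raises a second question: which comparison was it computed for?

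**Working it through.** **Inputs.** UC 4 %, IntS+A 18 %, IS 8 % or 12 %; 215 per arm; two-sided alpha 0.025 (chi-square, primary) and 0.05 (Fisher, secondary). All are from the two sample-size sections.

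**Formula.** For groups of n₁ and n₂ with rates p₁ and p₂, and pooled rate p̄ = (n₁p₁ + n₂p₂)/(n₁ + n₂):

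power = Φ{ (|p₁ − p₂| − z·s₀) / s₁ }, with s₀ = √[p̄(1 − p̄)(1/n₁ + 1/n₂)] and s₁ = √[p₁(1 − p₁)/n₁ + p₂(1 − p₂)/n₂].

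Here z = 1.960 for alpha 0.05 and 2.241 for alpha 0.025. Exact powers were also found by summing binomial probabilities over all outcomes that the test rejects. For the combined group these are sums over separate IS and UC binomials.

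**1. The stated 82 % (IS versus UC, 215 per arm).** Fisher's test is usually approximated with a continuity correction, which replaces n = 215 by the m that solves 215 = (m/4)·[1 + √(1 + 4/(m·d))]², where d = |p₁ − p₂|.

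- 12 % versus 4 %: m = 190.7, s₀ = 0.02778, s₁ = 0.02748. (0.08 − 1.960 × 0.02778)/0.02748 = 0.93, so power is **82.4 %**. This reproduces the plan's figure. Exact Fisher power is **84.5 %**.
- 8 % versus 4 %: m = 167.9, s₀ = 0.02592, s₁ = 0.02583. (0.04 − 1.960 × 0.02592)/0.02583 = −0.42, so power is **33.8 %**. Exact Fisher power is **34.4 %**.

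Between the two rates, the continuity-corrected power is 48 % at IS 9 %, 61 % at 10 % and 73 % at 11 %.

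**2. The stated 80 % (IntS+A versus IS and UC combined, 215 versus 430).** With equal arms the combined rate is the mean of IS and UC.

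- IS 8 %: combined (8 + 4)/2 = 6 %; p̄ = 0.100, s₀ = 0.02506, s₁ = 0.02860. (0.12 − 2.241 × 0.02506)/0.02860 = 2.23, so power is **98.7 %** (exact 99.1 %).
- IS 12 %: combined (12 + 4)/2 = 8 %; p̄ = 0.1133, s₀ = 0.02648, s₁ = 0.02929. (0.10 − 2.241 × 0.02648)/0.02929 = 1.39, so power is **91.7 %** (exact 92.6 %).

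Neither is 80 %.

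**3. What does give 80 %.** IntS+A versus IS alone, 215 per arm, alpha 0.025:

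- 18 % versus 8 %: p̄ = 0.13, s₀ = 0.03244, s₁ = 0.03208. (0.10 − 2.241 × 0.03244)/0.03208 = 0.85, so power is **80.3 %** (exact chi-square 81.1 %).
- 18 % versus 12 %: p̄ = 0.15, s₀ = 0.03444, s₁ = 0.03432. (0.06 − 2.241 × 0.03444)/0.03432 = −0.50, so power is **30.8 %** (exact 30.7 %).

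**Summary (exact powers)**

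| Contrast | Plan | IS 8 % | IS 12 % |
|---|---|---|---|
| IS vs UC, Fisher, 0.05, 215 per arm | 82 % | 34 % | 84 % |
| IntS+A vs IS and UC combined, 0.025, 215 vs 430 | 80 % | 99 % | 93 % |
| IntS+A vs IS alone, 0.025, 215 per arm | not stated | 81 % | 31 % |

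**The case against.** The strongest reply is that this is one mislabelled number. Since (12 + 4)/2 = 8, the 8 % may be the combined IS and UC rate written down as the IS rate. The basis section supports only 12 %, and the 82 % is reproducible at 12 %. On that reading the described primary comparison has about 93 % power and the secondary about 84 %, so nothing is lost and the sample size is sound.

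Much of this stands. A reader might infer that the two stated powers cannot both hold. The documents do not support that for the 215 versus 430 comparison they describe, because at IS 12 % both stated levels are reached. The two figures exclude each other only if the 80 % was meant for IntS+A versus IS alone, which is not the comparison the text names. A reader might also infer that IS versus UC is simply underpowered at 34 %. That depends on the less supported of the two rates. Nor does the remark that quit rates nearly doubled in those who stopped drinking count against 8 %: it compares drinkers with people who quit drinking in the earlier study, and sets no ratio between arms.

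Two things remain. The article nowhere says that 8 % is a combined rate; it assigns it to IS and lists UC separately at 4 %. And the mislabelling explanation does not rescue the 80 %, because the combined comparison at 8 % has about 92–93 % power.

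**Conclusion.** The point holds as an inconsistency in the planning inputs and an unreproduced primary power figure. It does not show that the trial is too small.

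- The IS rate is contradictory (8 % against 12 %), and the 82 % for IS versus UC depends on 12 %. At 8 % it would be 34 %.
- The 80 % for 215 versus 430 understates the power of that comparison by about 13 points at IS 12 % and about 19 points at IS 8 %. It agrees only with a pairwise IntS+A versus IS calculation at 18 % versus 8 %, which would fall to about 31 % at IS 12 %.

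This rests on equal arms of 215, the alphas and tests as stated, loss to follow-up counted as smoking, and reading the IntS label as IS. Which IS rate was intended, and which contrast the 80 % was computed for, only the sponsor can say.

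**What to change.** State one week-52 IS rate and use it in both power statements and in Basis for sample size. Correct the IntS label in the secondary power statement to IS. Confirm the primary contrast and restate both powers for it.

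- If IS is 12 % and the primary contrast is 215 versus 430: about 93 % primary and about 84 % secondary (exact Fisher). If 8 % was meant as the combined rate, label it so.
- If IS is 8 %: about 99 % primary and about 34 % secondary. Revise the basis section to justify 8 %, and do not describe IS versus UC as powered.
- If the intended primary contrast is IntS+A versus IS alone, say so; power is about 80 % at IS 8 % and about 31 % at IS 12 %.

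The cost is a text correction and two recalculations. For the 215 versus 430 comparison as described, the sample size does not change. The secondary power figure may become less favourable.
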